**Table T2:** 

Day 1	• Rapid PEER training workshop with Peer Interviewers
Day 2	• Peer Interviewers interview their friends
Day 3	• Peer interviewers interview their friends; Rapid PEER specialist de-briefs Peer Interviewers
Day 4	• Rapid PEER specialist debriefs remaining Peer Interviewers • Final workshop with Peer Interviewers
Following days	• Rapid PEER specialist undertakes desk-based data coding and analysis

## Evidence-informed policy dialogue

We will identify key state-level stakeholders during the formative research stage. We will then design a policy dialogue and stakeholder engagement process to inform future implementation during the subsequent two years. These activities will help us collaboratively design the intervention and create a communication space for exchanging program insights and results. This process ensures that the research itself not only adds value to existing initiatives, but that research decisions are widely discussed. It further increases a-priori program ownership and the odds that stakeholders will adopt results locally. Multi-stakeholder engagement processes, are based on empirical evidence generated by studies of the diffusion of innovations, comparative policy and political science studies, knowledge utilization and evaluation studies and the science of team science
^49–
55^. During the formative stage, the aim is to characterize the factors that affect how policymaking and normative change can mutually reinforce each other
^56^.

## Data collection

### Training

We will hold an in-person training in Bhubaneswar, Odisha. Researchers from the George Washington University will conduct the training alongside research staff from DCOR Consulting. Following the training, we will pilot test all instruments and research methods over the course of two days in Gandilo Village, Khurda District located about 45 minutes outside of Bhubaneswar. We will translate and review select KII and FGDs to ensure that the participants understand the research questions and interviewers are using the skills discussed during training. After all instruments are revised, trained researchers from DCOR Consulting will collect all data in person.

We will match interviewer/moderator by gender whenever possible to build interviewer rapport
^69^. We will conduct all interviews in Odia, the local language in locations selected by our local research partners in collaboration with local officials. Each interview and focus group will be audio recorded. DCOR consulting will transcribe the interviews and focus groups from Odia to English.

### Instrument development

We designed the data collection instruments (
Supplementary File 1 –
Supplementary File 4) based on the TNSB, a review of the literature on barriers and facilitators to IFA use, and feedback from the expert panel on our team. To explore IFA norms in a less personal and threatening way and to reduce social desirability bias within the focus groups, we will use vignettes, short stories about hypothetical characters who live in a rural village in Odisha. Vignettes are a simple way to explore social norms relating to a behavior
^70^. During the pilot study, we will test and revise all of the instruments as needed to ensure that the questions flow well, are culturally relevant, and capture the relevant constructs. The pilot study will also help to identify regional lexicon, which will inform revisions of the formative data collection instruments.

### Site selection

Within the state of Odisha, we plan to work in Angul district. We chose Angul for several reasons: 1) it is three hours from Bhubaneswar, the capital of Odisha, representing a rural but not isolated area 2) There are many existing SHGs 3) IFA supplements are available (as this is primarily a behavioral/demand side study); and 4) malaria and anemia rates are average compared to the rest of India. Within the district of Angul, we will conduct the formative research in the Athmalik block including four villages, two tribal and two non-tribal, Barham, Bardabar, Dudum and Tapadhol. We will also conduct the randomized control trial and intervention in Angul including but not limited to the villages from the formative research.

### Sample selection

Inclusion criteria are that participants must reside in the selected village because many of the questions pertain to norms in their communities. They must also speak either Odia or English, and they must be at least 15 years old.

### Sampling

The FGD sample will include WRA (both pregnant and not pregnant), husbands, and mothers-in-law. We plan to use a random sampling procedure to select participants for FGDs. Local Anganwadi health workers have a household enumeration of everyone who lives in each village. Based on the number of individuals needed for FGDs, against a sampling frame that will consist of the entire village, we will use a proportional skip pattern that begins with a randomly selected initial participant in order to identify households from which to select every succeeding participant for each category (e.g., mothers in law, husbands and WRA).

For the perceptual mapping exercise, we will use the same random sampling method (at the village level) and participants are only eligible to participate in one research method.

Among the key informant interviews, SHG leaders, Odisha Health Officials, teachers, and health providers, we plan to specifically employ critical case or “reputational” sampling where cases will be chosen based on specialized knowledge or expertise. These interviews will be conducted with individuals who have expertise with respect to a specific perspective on this issue
^71,
72^. Therefore, we will conduct key informant interviews with SHG leaders, ANC clinic providers who serve pregnant and reproductive age women, health officials who work on anemia or IFA distribution/education in Odisha and front line IFA dispensary workers. This sampling strategy will ensure that we interview the most knowledgeable key informants. Our sampling strategy will be refined in consultation with our local partners and Anganwadi health workers, who will recommend key informants who meet these criteria.

We will conduct Rapid PEER interviews in two villages within the selected district. In each site we will purposively choose six PEER interviewers (one each from women of reproductive age (15 – 25 years old), women of reproductive age (26 – 49 years old), pregnant women (15 – 49 years old), younger married men (15 – 25 years old), older married men (26–49 years old) and mothers-in-law). Each interviewer will interview or hold conversations with two interviewees (with same-sex friends who fit the previously discussed inclusion criteria). Within the two villages, we will train 12 PEER interviewers who will conduct 24-interviews.

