### Research methods and analysis

***Aims and objectives***. By the end of the formative assessment period, we will have designed, adaptively tested, and refined an intervention that can be feasibly and effectively implemented to reduce iron-deficiency anemia among women of reproductive age and pregnant women in Odisha, India. To achieve this goal, the formative assessment has the following aims:

1. At the community level, to identify key contextual, administrative, policy, and service environments that either facilitate or hinder access to and use of IFA supplements among women of reproductive age and pregnant women2. At the interpersonal and individual levels, to identify norms, referent groups, and the extent to which they act as barriers or facilitators to IFA use and compliance among reproductive age women and pregnant women3. To design, pilot test, and subsequently modify and finalize an intervention to increase IFA use and compliance and to reduce anemia among reproductive age women (with a focus on transforming harmful norms and promoting beneficial norms)

The formative assessment will be conducted from March to December, 2018. After analyzing results, we will hold a convening workshop in July, where we will formulate a first draft of the intervention plan. We will pilot test the various components of the intervention to determine its feasibility and effectiveness. Findings from these pilot evaluations will inform and refine the intervention, which we will finalize by December, 2018.

Figure 1 depicts the formative research workflow.

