## Research setting

### Odisha, India

Odisha is an eastern Indian state on the Bay of Bengal (
Figure 2). According to the 2015–2016 India Demographic Health Survey, 83% of households in Odisha reside in rural areas and 67% of women and 84% of men are literate. The vast majority of household heads are Hindu (95%) and 23% of households belong to a specific tribal culture. The total fertility rate (TFR) in Odisha is 2.1 children per woman. In the last five years, 60% of pregnant women had four or more antenatal care visits and 82% of women delivered in a health facility. About half (51%) of women in Odisha have anemia with a higher rate for women from a tribal culture, those following the Christian faith, and those with no schooling
^58^.

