### Data collection modalities

We will collect qualitative data via in-depth interviews, focus groups, Participatory Ethnographic Evaluation and Research (PEER) interviews, and structured observations.

***In-depth interviews and focus groups.*** We will conduct in-depth interviews with key informants including Self-help group (SHG) leaders, health providers, teachers and health officials. We will conduct focus groups with women of reproductive age (including pregnant women), spouses, mothers, and mothers-in-law. Prior to focus group interviews participants will complete a demographic questionnaire including questions about caste. We plan to conduct approximately sixteen focus groups and twenty-four key informant interviews but the final sample size will be determined based on theoretical saturation
^64^.
Table 1 shows the expected number of interviews and focus groups.

**Table 1. T1:** Expected Number of interviews and focus groups. Preliminary Schedule of Focus Group Discussions (FGDs) and In-depth Interviews (IDIs).

Participants	Session type	# Sessions	# Participants
Self-help group leaders	IDI	4	1
Government/ministry representatives	IDI	4	1
Antenatal service providers	IDI	4	1
Secondary school teachers	IDI	4	1
Traditional Healers	IDI	4	1
Anganwadi/ASHA workers	IDI	4	1
Adolescents of reproductive age (15 – 19) years old	FGD	4	6–10
Women of reproductive age (20 – 35) years old	FGD	4	6–10
Married men (18 – 42) years old	FGD	4	6–10
Mothers-in-law	FGD	4	6–10

***Observational Data.*** Observation can allow the researcher to draw inferences about a phenomenon that they cannot obtain from direct conversation via interviews or focus groups. We will collect observational data from four venues: antenatal care (ANC) clinics, medicine stores/pharmacies, self-help groups, and outdoor food markets. Data collectors will take notes on a standard observation form (See
Supplementary File 3) at one of each of the following four venues in each of the four villages (16 observations total):

Medicine store/pharmacy observations will note how well IFA tablets are stocked, where they are stocked within the store, the extent to which they are purchased, their price, and their packaging.

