*p*-dimensional plane, thus showing the relative distances among behaviors or objects. Two behaviors or objects close to each other on a particular attribute signify their conceptual proximity. This mapping provides an understanding about how the primary behaviors or objects of interest are understood by the audience; it also specifies the relative distances among objects.

Three perceptual mapping exercises will be conducted: one among women of reproductive age (including pregnant women), one among men (who constitute the support group for the women), and one among mothers/mothers-in-law and sisters or sisters-in-law. Approximately 30 individuals per group will participate in the mapping exercise, for a total of 90 individuals.

***Rapid PEER.*** We will also conduct Rapid Participatory Ethnographic Evaluation and Research interviews (Rapid PEER), which will enable us to gain local insights into the beliefs and behaviors of beneficiaries, in the full context of their lived experience. This unique ‘insider perspective’ will ensure intervention is truly designed with the user in mind. We will train ‘ordinary’ members of the target group, in this case pregnant women and women of reproductive age, their spouses, and their mothers/mothers-in-law, after which they will serve as Peer Interviewers
^67,
68^.

To execute the Rapid PEER, we will train Peer Interviewers to carry out in-depth conversational interviews designed to obtain targeted information from others in their own social group. We will decide on five key questions that form the structure of the conversational interview process. The Peer Interviewers themselves will suggest how to form the questions from formal Odia language into a more conversational format. Non-literate Peer Interviewers will draw pictures to represent each of the five questions. We will ask the same questions at each site to at least two interviewees from the PEER interviewers social group. The informal wording and pictures to remember and ask the question may vary to suit the preference of the Peer Interviewers.

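### Whole-village random sampling with no stated pregnant category would yield only about 3 to 8 pregnant women in the focus groups and mapping, although Aims 1 and 2 name them

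*Protocol article*

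**What the plan says.** Under Research methods and analysis, Aim 1 concerns access to and use of supplements in women of reproductive age and in pregnant women. Aim 2 concerns norms and referent groups as "barriers or facilitators to IFA use and compliance among reproductive age women and pregnant women". Pregnant women are thus named in both aims.

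Under Sampling, the article promises both kinds of women: "The FGD sample will include WRA (both pregnant and not pregnant), husbands, and mothers-in-law". The procedure is a village enumeration held by Anganwadi workers, a random start, and then "against a sampling frame that will consist of the entire village, we will use a proportional skip pattern", which leads to "every succeeding participant for each category (e.g., mothers in law, husbands and WRA". Pregnant women are not among the categories given as examples.

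Table 1 (Data collection modalities) divides the women's focus groups by age only: "Adolescents of reproductive age (15 – 19) years old" and "Women of reproductive age (20 – 35) years old", each with four sessions of 6-10 people. Perceptual mapping has three groups of about 30, "one among women of reproductive age (including pregnant women"; the Sampling section applies the same random method to it and lets each person join only one method.

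Pregnant women are a reserved category only in Rapid PEER: one pregnant interviewer, purposively chosen, in each of two villages. The two friends each interviewer talks to need only be of the same sex and fit the general inclusion list, so they need not be pregnant.

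**The concern.** A proportional skip gives each subgroup its population share and no more. Few women are pregnant at any one time, so a random sample of this size will contain few of them unless places are set aside.

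The article itself gives reasons to treat pregnancy separately. Supplementation is daily in pregnancy and weekly otherwise. Some reported beliefs, such as that too much iron makes for a large baby and a harder labour, belong to pregnancy. The cited work on husbands and mothers-in-law concerns pregnant women, and norms are said to limit uptake particularly in pregnancy. If very few currently pregnant women are heard, saturation could be declared on themes raised mainly by non-pregnant women, and the intervention is to be finalised from these data.

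**Working it through.** **1. Planned counts reproduce.** Four focus-group categories x 4 sessions = 16. Three mapping groups x 30 = 90. Rapid PEER: 2 villages x 6 = 12 interviewers, x 2 = 24 interviews. All agree with the article, which gives no expected number of pregnant women.

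**2. Women sampled at random.** Focus groups: 2 women's rows x 4 sessions x 6-10 = 48-80. Mapping: about 30. Total: 78-110.

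**3. Share pregnant at one time.** The article's input is "The total fertility rate (TFR) in Odisha is 2.1 children per woman" (Odisha, India). The assumption is 0.75 year per pregnancy, ignoring losses. Share = births per woman x 0.75 / years of exposure.

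- Births even over ages 15-49: 2.1 x 0.75 / 35 = 4.5%.
- All births at 15-35: 2.1 x 0.75 / 21 = 7.5%.
- Ages 20-35, with an assumed 75-90% of births there: 2.1 x 0.75 x 0.75 / 16 = 7.4%, to 2.1 x 0.90 x 0.75 / 16 = 8.9%.
- All births at 20-35 (extreme bound): 2.1 x 0.75 / 16 = 9.8%.

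**4. Expected number in both random methods together.**

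- At 4.5%: 78 x 0.045 = 3.5 to 110 x 0.045 = 5.0 (binomial 5-95% range 1-7 at n = 78 and 2-9 at n = 110).
- At 7.5%: 78 x 0.075 = 5.9 to 110 x 0.075 = 8.3.
- At the 9.8% bound the adolescent groups contribute none. The 20-35 groups give 24 to 40 x 0.098 = 2.4 to 3.9 and mapping at most 3.0, so about 5 to 7.

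The range is therefore roughly 3 to 8.

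**5. Focus groups at ages 20-35.** Across all four: 24 x 0.074 = 1.8 to 40 x 0.089 = 3.5 pregnant women. Chance that a group of eight has none: (1 - 0.074)^8 = 54% to (1 - 0.089)^8 = 48%.

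**6. Mapping group of 30.** The article gives no age limits for this group. At 4.5%: 30 x 0.045 = 1.35 expected and 0.955^30 = 25% chance of none. If it were confined to ages 20-35: (1 - 0.074)^30 = 10% to (1 - 0.089)^30 = 6%.

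**7. Could a larger sample cure this?** To expect 24 pregnant women, the size of four focus groups of six, the stated scheme would need 24 / 0.045 = 534 sampled women, or 24 / 0.075 = 320.

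**The case against.** **The categories are only examples.** The list is open and omits adolescents, who do have a row in Table 1, and the text says that pregnant women will be included. This stands to the extent that a pregnant category is not ruled out; a reader might infer that the plan excludes one, and it does not. But none is stated, Table 1 has none, and the remark about refining the sampling strategy closes the paragraph on key informants.

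**The design is adaptive.** Table 1 is preliminary, the final number of sessions depends on saturation, and analysis runs alongside collection. Thin coverage could be noticed and corrected. Nothing in the plan requires that, however, and step 7 shows that more sampling by the same rule is not a practical cure.

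**Other sources speak to pregnancy.** A reader might infer that barriers specific to pregnancy cannot be identified at all. The document does not support that. Women who were recently pregnant may be among the 20-35 groups. There are four interviews with antenatal providers and four with Anganwadi/ASHA workers, four antenatal-clinic observations, and eight focus groups of husbands and mothers-in-law. Vignettes ask about community norms, which a woman need not be pregnant to describe, and the sources are triangulated. The two pregnant PEER interviewers may also choose pregnant friends, up to four. All of this softens the consequence, but it does not replace direct evidence from a group named in the aims.

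**Under-filled groups.** A reader might also infer that a whole-village skip leaves the adolescent and mother-in-law groups short, by landing on households with no eligible member. The text does not support this: selection is per category and tied to the number needed, and nothing says that an ineligible household uses up a place.

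**The share is uncertain.** It applies a state fertility rate to four villages, two of them tribal, and 4.5% is the low end for women under 36. That is fair, and is why the ranges are shown.

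**Conclusion.** The point holds as one of coverage and saturation in a qualitative study; statistical power is not at issue. Followed as written, the sampling rule would bring in roughly 3 to 8 currently pregnant women among 78-110 women, spread over eight focus groups and one mapping group, plus two pregnant PEER interviewers. About half of 20-35 focus groups of eight would have none.

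This rests on the state fertility rate, an assumed 0.75-year pregnancy, an assumed age spread of births, and treating the skip as a simple random draw. Across shares from 4.5% to the extreme bound of 9.8% the conclusion does not change. Evidence taken directly from pregnant women would be thin, and whether saturation had been reached for them would be hard to judge. The plan should be changed here, but the study would not be without information on pregnancy.

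**What to change.** In the Sampling section and Table 1:

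- Draw up separate lists from the Anganwadi enumeration: pregnant women, non-pregnant women by age band, husbands, mothers-in-law. Run the skip within each list.
- Set a minimum number of pregnant women for each 20-35 focus group and for the women's mapping group, within the planned totals. For mapping this could be up to about 10 of the 30 places.
- State the minimum as subject to village numbers. Village sizes are not given, and no one may join two methods. At 4.5%, ten pregnant women for mapping imply about 10 / 0.045 = 222 resident women aged 15-49 across the villages used, before the focus groups and PEER draw on the same women.
- Report saturation for pregnant women separately.

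The cost is list preparation and a few sentences, with no extra sessions or participants. The women's sample would no longer be proportional to the village and would include fewer non-pregnant women. With ten reserved mapping places, 20 non-pregnant women remain instead of an expected 30 - 1.35 = about 29 at the 4.5% share. Making whole focus groups pregnant-only is not needed: doing so for two of the four 20-35 groups would halve that age band's sessions with non-pregnant women.

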## Analysis

We will use an iterative approach to data collection and data analysis, whereby analysis and data collection will happen concurrently. This will allow us to determine when thematic saturation occurs and no new themes are emerging from the data
^56^. Initially, we will read transcripts and create memos, written logs used to capture reflection and analytic insights (Groenewald, 2008)
^73^. Findings from all data collection sources, semi-structured interviews, Rapid PEER interviews, focus groups, observation, and perceptual mapping, will be triangulated to examine whether or not these different methods support the same identified themes. Using different data sources will also allow us to gain information about different aspects of the phenomenon
^74^.

Following the procedures outlined by Guest
*et al.*, 2011
^75^, we will conduct applied thematic analysis to characterize the knowledge, attitudes and behaviors relevant to IFA use. We chose applied thematic analysis because our overall study aim, to inform an anemia reduction intervention, is applied in nature. Experienced qualitative researchers from both The George Washington University and DCOR Consulting will independently review transcripts to develop an initial codebook and modify the codebook as themes emerge. We will use both inductive and deductive coding to categorize concepts. Specific a priori codes will be used to identify text related to our research questions and additional codes will be added to the codebook based on new themes that emerge during coding. Using NVivo v.11, we will identify themes by comparing codes and content across sources, and by running specific word queries, associations between themes, and creating hierarchal visual displays of codes to identify linkages and patterns in the data.

We will analyze perceptual mapping data with multidimensional scaling techniques, which seek commonalities in responses that can be clustered together into groups, much like factor analysis, that have low intra-group and high intergroup variances. First, we will map clusters on a multiplane axis and iteratively identify the underlying dimension. Next, we will compare emerging dimensions with themes emerging from the qualitative analysis. Lastly, we will discuss and identify the underlying dimension with the highest validity and intervention utility.

Finally, we will use matrix analysis as a tool to display and further develop our results. Identified themes will be organized using descriptive matrix analyses that visually display the range of related responses
^76^. This will allow for a comprehensive analysis of the data and ensure that we not only focus on the majority responses among participants, but also the outliers.

We will analyze the Rapid PEER interviews following these steps:

To keep the conversation flowing, the Peer Interviewers will not take notes during the interviews but simply remember the conversation. Shortly after the interviews (the same day or the next day), the facilitator from the study team will meet and ask the Peer Interviewers about what their friends said about the topic. The facilitator will take detailed notes during these de-briefing sessions.The notes (originally written in Odia) will be translated verbatim in English. After translation, the research team will read all of the notes and identify the primary themes that emerged from the interviews. Next, they will assign themes to text segments.They will then identify relevant barriers and facilitators to IFA use and select illustrative quotes to include in a final report.

To test the validity of our findings and the existence of potential threats to those conclusions, we will conduct several validity checks including:

*Long-term involvement in the community.* Our formative research is planned to continue for six months to provide adequate time to pilot test and tailor the data collection instruments, to return to follow up on initial findings, to provide adequate time to complete data collection and to reach thematic saturation.
*Rich data.* We will use verbatim transcripts of the interviews and focus groups as well as descriptive notes for the perceptual mapping and observation.
*Respondent validation.* We will hold a convening in Odisha to present and get feedback on our findings from participants, key stakeholders and research partners.
*Triangulation.* We will triangulate our data by collecting data from a diverse range of individuals and use a variety of data collection methods. Additionally, our research teams have diverse backgrounds and bring multiple perspectives to the data analysis. Researchers from both GWU and DCOR consulting will co-analyze data.

Throughout the design, data collection and analysis, we will refer to the consolidated criteria for reporting qualitative research (COREQ): a 32-item checklist for interviews and focus groups to ensure study rigor and credibility
^77^. The quality of study reporting has been improved through formal reporting frameworks, like the COREQ
^78^.

Strengths and limitations of this studyThis study will provide evidence-based recommendations to guide the development of a social norms-based anemia reduction intervention.This study will explore multilevel (individual, interpersonal, community, and environment) barriers and facilitators to iron and folic acid uptake and compliance.We will conduct this efficacy trial in one state in India. Therefore, generalizability may be limited.

